**Primary clinical outcome measure**

**iHOT-12**

The iHOT-12 is a patient reported outcome of Quality of Life (QoL) [43] and will be the planned primary outcome measure for this study. This shorter version of the original iHOT-33 was developed and validated for patients with FAIS and was found to be valid, responsive and a reliable tool to measure the impact of hip disease in young active individuals on QoL [43].The minimal clinical important difference for the iHOT-12 is 13.0 and patient acceptable symptom state threshold is 63.0 for FAIS [44].

**Secondary clinical outcome measures**

**Muscle strength using Handheld dynamometer**

Several studies have discussed the implications of reduced muscle strength in the hip and how this could predispose to lower extremity injuries [45-47]. A recent systematic review evaluating muscle strength measurement in various hip pathologies reported that there is evidence of bilateral hip muscle weakness regardless of whether the hip joint is symptomatic or not [48]. Both motor driven and hand-held dynamometry (HHD) are reliable methods of muscle strength measurement and should be used with make tests (where the patient pushes against the examiner’s fixed resistance) [48]. Due to the pragmatic nature of this study HHD will be used. HHD with an external belt fixation has shown good inter-tester reliability with intra-class coefficient of 2.1 (range 0.76 to 0.95) [49]. Maximum voluntary isometric contraction will be utilised as the measurement for all hip muscles groups [50]. A minimum detectable change (MDC) score is often used to detect real change in an outcome measure overtime [51]. An MDC value at 95% CI ranging from 9-45 points was reported for individual hip muscle groups in healthy subjects using a HHD showing it is responsiveness [52]. Further details on how to perform the tests are described in supplementary Appendix 1.

**Star Excursion Balance Test (SEBT)**

The SEBT is a reliable measure to assess dynamic postural control and proprioception and has shown excellent inter-rater reliability [53]. The SEBT has shown good criterion and divergent validity in relation to pain, hip strength and ROM in patients with FAIS [54, 55]. See supplementary Appendix 1.

**Brief Pain Inventory-short form (BPI)**

Most patients with FAIS experience pain in the hip or groin [56], often chronic in nature. BPI is a multidimensional scale that can reliably measure chronic pain and its interference with an individual’s physical and social functioning [57]. The tool is responsive to change in pain associated with pharmacological, physical as well as psychological interventions and was recommended by the Initiative on Methods, Measurement, and Pain Assessment in Clinical Trials [58].

**Hospital Anxiety and Depression Scale (HADS)**

Recent studies have shown the prevalence of anxiety and depression in patients undergoing hip arthroscopic procedures [15, 36]. Previous studies have reported improvements in the level of anxiety and depression experienced by patients when undergoing prehabilitation [59, 60]. The HADS scale is a validated tool to measure anxiety and depression in general medical population of patients and will be utilised in the study [61]. A literature review including 747 papers reported a sensitivity and specificity of 0.8 at a cut off score of >8 on HADS which was very similar to other health questionnaires [62].

**Patient’s Global Impression of change (PGIC)**

The Global rating of change (GRC) scales are often used in research particularly within the musculoskeletal area[63]. Among the GRC scales, PGIC scale is frequently used to gather a patient’s perception of change after an intervention. The scale typically consists of 7 points which depicts a patient’s overall improvement from “very much improved” to “very much worse[64]. These scales have shown adequate reproducibility and sensitivity to change in a variety of disorders , and are easy to use and interpret[63].

**Data analysis**

Data will be analysed using SPSS version 28. Descriptive statistics, such as percentages (for rate calculations), means, standard deviations and mean change (if data are normally distributed) will be analysed to evaluate the distribution of scores. Standard deviations and effect sizes for outcome measure data will be used to calculate the required sample size for a definitive trial in the future.

All transcribed qualitative data will be thematically analysed [65]. The Personal assistant to the Chief investigator will be responsible for the transcriptions. As a member of staff, they will follow all the protocols of confidentiality and information governance procedures as per the host hospital's policy. Once used, all original recordings will be deleted. Transcripts will be reviewed by the participants prior to analysis by the researchers using Nvivo software[66]. For credibility and confirmability of the qualitative data, coding and themes will be analysed by the PI and primary academic supervisor ([name]).

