**Methods**

This feasibility trial protocol is registered with ISRCTN Registry No. [15371248](https://gbr01.safelinks.protection.outlook.com/?url=https%3A%2F%2Furldefense.com%2Fv3%2F__https%3A%2Fgbr01.safelinks.protection.outlook.com%2F%3Furl%3Dhttps*3A*2F*2Fwww.isrctn.com*2FISRCTN15371248%26data%3D05*7C01*7Canuj.punnoose*40nhs.net*7C9fa1d1cb31ac4eea522208db208040f0*7C37c354b285b047f5b22207b48d774ee3*7C0*7C1*7C638139507488348179*7CUnknown*7CTWFpbGZsb3d8eyJWIjoiMC4wLjAwMDAiLCJQIjoiV2luMzIiLCJBTiI6Ik1haWwiLCJXVCI6Mn0*3D*7C3000*7C*7C*7C%26sdata%3DjhuBzsDF9dAXwZp2WybtzoFfhM2QmT*2BD5nBgph95ur8*3D%26reserved%3D0__%3BJSUlJSUlJSUlJSUlJSUlJSUlJSUl!!NLFGqXoFfo8MMQ!o5gyU8Yg-xtoOcV03CIwwOj7buBTB7wtM4htRAAEHbePs9xDAJES7cOV8pIh9cNPci9izQN619tq1p8G25HStGs06plu7McpEOMnDzY%24&data=05%7C01%7Canuj.punnoose%40nhs.net%7C7ea3de2b1fe449cc8fce08db208cf620%7C37c354b285b047f5b22207b48d774ee3%7C0%7C1%7C638139562080717319%7CUnknown%7CTWFpbGZsb3d8eyJWIjoiMC4wLjAwMDAiLCJQIjoiV2luMzIiLCJBTiI6Ik1haWwiLCJXVCI6Mn0%3D%7C3000%7C%7C%7C&sdata=qUiiP46We8crUy1mnwHx6QBKHD8yqnz7a3Iu3yI%2BYI4%3D&reserved=0) and reported as per  CONSORT 2010 statement: extension to randomised pilot and feasibility trials to ensure transparency and reproducibility [30]. All patient and public involvement meetings will be evaluated using an Impact log and reported in line with the GRIPP2 short form reporting checklist [31].

This feasibility trial will use a mixed methodology encompassing the following;

- A quantitative two arm parallel group feasibility trial
- Embedded qualitative component (Physiotherapists & Research participants) using thematic analysis

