**Trial component**

A prospective two group parallel feasibility trial will be conducted to answer the above trial objectives [27].

Outcome measures will be obtained at baseline (prior to prehabilitation intervention), after prehabilitation before surgery, and at 6 weeks+/- 4 weeks and 6 months+/- 4 weeks (planned primary endpoint for definitive RCT) postoperatively when participants attend the research site for clinical care. Additionally, all patient reported outcome measures will be captured at 12 months+/-4 weeks post-op (secondary end point). Physical outcome measures will be taken onsite during the participant’s clinical visits and patient reported outcomes will be collected via the Physitrack app (<https://www.physitrack.com/clinical-studies>) or mailed to the participants at various follow-up points (see Fig. 2).

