**Sample Size**

An overall participant sample of 50-60 (25-30 per arm) is recommended to estimate standard deviations for calculating sample size required for a full trial [69]. As a tertiary referral centre for hip arthroscopies, 350-375 new patients are referred to the service every year out of which an estimated 120 hip arthroscopies are performed/year.

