**Limitations of the study**

- The number of study participants has been selected to test efficacy and feasibility to be able to perform a sample size calculation to determine the number of participants required for a definitive trial. Therefore, these results should be considered as preliminary findings.
- Study is conducted in a single tertiary hospital and therefore may need to be adapted prior to wider implementation.

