**Table 1. Study objectives and success criteria**

| General objectives | Success criteria |
| --- | --- |
| Recruitment procedure | Participants were recruited within the time constraints of the local NHS hospital |
|  | Participants report that there were no challenges with the recruitment procedure |
| Data collection methods | Data completeness of ≥80% |
|  | Patients and assessors reported that there were no challenges with the data collection methods |
| Follow-up procedures | 100% of participants were contacted for follow-up |
|  | ≥80% completion of follow-up outcome measures |
| Specific objectives | **Success criteria** |
| *Feasibility* | |
| Participant recruitment rates | The recruitment rate of this study will be considered sufficient if at least 33% of eligible patients are recruited over a period of 18 months (n=60). |
| Attrition rate | <30% dropout |
| Usability of Physitrack | Patients and Physiotherapists reported no challenges with the use of Physitrack and telehealth system. |
| Capacity (time and effort) of clinicians to deliver the programme | Physiotherapists report that they had adequate time and resources available to deliver the programme |
| Treatment fidelity | ≥80%  completion of the self-reported checklist |
|  | Physiotherapists reports that there were no barriers identified in the use of self-reported checklists. |
| *Suitability* | |
| Outcome measures | Patients and assessor report that the outcome measures were appropriate and self-explanatory |
|  | Data completeness of  ≥80% |
| Adherence to the programme | ≥70%  of the sessions (face to face + home ex monitored by Physitrack) |
| Time required to undertake each stages of the study | Physiotherapists report that they had enough time to complete each stages of the study. |
| Service infrastructure | Recruitment targets met  Data completeness of ≥80%  Clinicians and researchers report that there was adequate infrastructure to allow completion of a full trial. |
| *Acceptability* | |
| Intervention | Patients and clinicians report that the programme was appropriate and satisfactory |
| Randomisation | Patients are willing to be randomised for a future definitive trial.  (≥80% ) |
| Safety | |
| Intervention | Patients report that the intervention was safe, and no serious adverse events occurred during the prehabilitation phase. |

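### The definitive trial is to be sized partly on effect sizes observed in this 50-60 participant study, although that number is justified only for estimating standard deviations

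*Protocol*

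**What the plan says.** Determining the sample size of a full trial is one of the protocol's General Objectives. Three sections bear on how that will be done.

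- Data analysis: "Standard deviations and effect sizes for outcome measure data will be used to calculate the required sample size for a definitive trial". The effect sizes come from this study's outcome data and stand beside the SDs as inputs.
- Sample Size, on the basis for recruiting this many: "An overall participant sample of 50-60 (25-30 per arm) is recommended to estimate standard deviations for calculating sample size required for a full trial". Only SDs are named.
- Limitations of the study, on how that figure was chosen: "The number of study participants has been selected to test efficacy and feasibility to be able to perform a sample size calculation". This gives a different purpose for the same number.

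The outcome concerned is the iHOT-12, which "will be the planned primary outcome measure for this study", with six months after surgery as the intended primary time point of the definitive trial. The iHOT-12 section also states that "The minimal clinical important difference for the iHOT-12 is 13.0", but no section makes this the difference that the definitive trial should detect.

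**The concern.** A sample size needs an SD and a target difference. A feasibility study can supply the first with usable precision. The second should be a difference worth detecting, set on clinical grounds. If it is the difference that happened to be observed, the error in that estimate passes into the sample size, and because the difference enters as an inverse square, the error is magnified.

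The sample of 50-60 is given no precision basis for an effect estimate anywhere in the protocol. No confidence limit, shrinkage or other allowance for error in the observed effect is mentioned. A chance-high effect would lead to an underpowered definitive trial. A chance-low one would lead to a trial far larger than needed, and a non-positive one would give no usable sample size.

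**Working it through.** **The plan's own figures.** The 50-60 is a recommendation from a cited source with no alpha, power, effect or precision target, so no formula reproduces it. The recruitment target in Table 1 ("at least 33% of eligible patients are recruited over a period of 18 months (n=60") can be checked: 120 arthroscopies a year x 1.5 years = 180, and 33% x 180 = 59.4. This agrees with 60 if every arthroscopy patient is eligible, but it says nothing about precision.

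**Inputs.** From the protocol: two parallel arms, 25-30 per arm, and 13.0 iHOT-12 points, used here only as an illustrative true difference. Assumed, because the documents do not give them: SD 25 (range 20-30), two-sided alpha 0.05, 90% power.

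**Step 1: correct size if the true difference is 13.** n per arm = 2(1.960 + 1.282)² (SD/13)² = 21.01 (SD/13)².
- SD 20: 50
- SD 25: 78
- SD 30: 112

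**Step 2: precision of the observed difference.** SE = SD x √(2/n). At SD 25 and 30 per arm, SE = 25 x √(2/30) = 6.45. With t(0.975, 58 df) = 2.002, the 95% half-width is 12.9 points. It is 10.3 at SD 20 and 15.5 at SD 30. With 25 per arm and SD 25 it is 2.011 x 7.07 = 14.2. The half-width is therefore about as large as the difference itself.

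**Step 3: sizing on the observed effect.** Simulate the observed difference as normal with mean 13 and the SE above, and the observed SD from a scaled chi-square on 58 df. Put both into the Step 1 formula and compare with the correct n. Alpha and power cancel from this ratio, so the error rates do not depend on them. Results for 30 per arm:

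| SD | Correct n per arm | Within 20% | Under half | Over double, or effect not positive | Outside a factor of 2 |
|---|---|---|---|---|---|
| 20 | 50 | 20% | 16% | 23% | 39% |
| 25 | 78 | 16% | 21% | 28% | 49% |
| 30 | 112 | 13% | 25% | 31% | 56% |

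At SD 25 the 10th to 90th percentile range is 28 to about 580 per arm, counting a non-positive effect as an infinite n. Among positive results only, the upper figure is about 447.

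**Step 4: fixing the difference and estimating only the SD.** At SD 25 the 10th to 90th percentile range is 60 to 97 per arm. The result is within 20% of the correct n in about 72% of studies, and misses by a factor of 2 in about 0.1% or fewer.

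**Step 5: attrition.** Table 1 tolerates dropout of just under 30%. At that edge 60 x 0.7 = 42 participants remain, or 21 per arm. At SD 25 the 10th to 90th percentile range for sizing on the observed effect becomes 24 to more than 1,300 per arm, and about 13% of studies fall within 20%.

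**Step 6: is 13.0 a safe substitute?** The Introduction quotes a between-group difference of 6.8 points (95% CI 1.7-12.0) on the parent iHOT-33, for arthroscopy against physiotherapy. That whole interval lies below 13.0. If the true difference were 6.8, a trial sized for 90% power at 13.0 would have power Φ(3.242 x 6.8/13 - 1.960) = Φ(-0.264), about 40%, whatever the SD. At SD 25 the required size would be 21.01 x (25/6.8)² = 284 per arm, not 78.

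**The case against.** The strongest case against has four parts.

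- **The study calls itself preliminary.** The Limitations section says so, the Data analysis sentence does not say the point estimate will be used alone, and an analysis plan that is not shown could add detail. This bears on severity. It does not remove the point, because the protocol sentence itself names observed effect sizes as an input and nothing in the protocol qualifies it.
- **Every magnitude rests on an assumed SD.** This is correct, which is why ranges are shown. The imprecision is substantial across the whole range.
- **A reader might infer that the plan yields a wrong sample size more often than not.** Across SD 20-30 that holds only if wrong means more than 20% out. Beyond a factor of 2 the miss rate is 39-56%, so it is not a majority throughout. Nor would the definitive trial usually be underpowered: the chance is close to one half.
- **A reader might infer that 13.0 should simply be imposed as the target.** The iHOT-12 section does not present it as a between-group difference, and Step 6 shows that it could itself produce an underpowered trial. The iHOT-33 figure is on a different scale and compares different treatments, whereas here both arms have surgery, so 6.8 is not a direct substitute either.

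It is also fair to say that using this study's SDs is sound and already planned, and that no Table 1 criterion depends on the observed effect. The documents therefore do not support a claim that a chance-low result would, by rule, lead to the intervention being dropped.

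**Conclusion.** The point stands in this form: the protocol uses an observed effect for a purpose that its sample size was not chosen to serve, and its sections disagree on what that sample size is for. With a true difference of 13 points and SD 20-30, the resulting definitive n would be within 20% of the correct figure in only 13-20% of studies of 30 per arm, against about 72% with a fixed difference. These rates depend on the assumed ratio of difference to SD and on the number analysed, while the weakness of the method does not depend on any one value. Severity is should-fix: a stated objective is affected, but the conduct of this study, its data collection and its Table 1 success criteria are not, and the needed SDs will be collected anyway.

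**What to change.** 1. In Data analysis, remove effect sizes as an input. State that the definitive trial will be sized on a between-group difference in iHOT-12 at 6 months, specified in advance and justified independently of the effect observed here. The 13.0 points are one candidate, but their suitability as a between-group target must be argued, given the smaller between-group figure in the Introduction.
2. State that this study supplies the SD, with an allowance for its uncertainty, and the attrition rate. Which confidence limit to use for the SD, and whether to take it from a baseline-adjusted model, are optional refinements that can be left to the analysis plan.
3. State that observed between-group differences will be reported with 95% confidence intervals as descriptive only.
4. In Limitations of the study, remove the statement that the number was chosen to test efficacy, so that it agrees with Sample Size. The similar efficacy wording under Strengths of the study can be edited at the same time.

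The cost is a few sentences of protocol text, with no new data, visits or participants. The downside is small: a target has to be justified before results are seen, and the definitive trial may turn out larger.

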**Data storage**

Study data will be collected and managed using REDCap electronic data capture tools hosted at the host institution. Additionally, personal data of participants will be stored securely on EDGE- a clinical research management platform approved by the host institution and will follow GDPR (General Data Protection Regulations) guidelines. All personal data used for the study will be destroyed at the end of the study. Anonymised quotations from the respondents might be used for dissemination such as peer reviewed publications or conferences. No single patient data will be reported or published ensuring confidentiality.

**Sample Size**

An overall participant sample of 50-60 (25-30 per arm) is recommended to estimate standard deviations for calculating sample size required for a full trial [69]. As a tertiary referral centre for hip arthroscopies, 350-375 new patients are referred to the service every year out of which an estimated 120 hip arthroscopies are performed/year.

**End of the study**

The end of the study will be declared when the last participant in the study has completed their 1-year post-op follow-up.

# **Discussion**

Despite the exponential growth and development of innovative surgical interventions for FAIS, it is estimated that nearly half (49%) receiving hip arthroscopy do not achieve optimal outcomes [9]. Deficits in muscle strength and ROM in patients with FAI is well evidenced in the literature [14, 70]. Additionally, pandemic outbreaks like COVID-19 has placed an unprecedented delay on elective operations leading to further chronicity and deconditioning in patients [71]. Therefore, optimising patients through effective prehabilitation programmes might play a vital role in early identification of impairments and promote physical and psychological wellbeing prior to undergoing surgery [72]. However, the role of exercise interventions prior to surgery in FAIS is under explored. This study will provide important preliminary data to inform feasibility of a definitive RCT in the future to evaluate effectiveness of a novel prehabilitation intervention. Additionally, the study will record compliance, adverse effects and satisfaction of the prehabilitation programme which are important elements at the feasibility stage [24].

It is anticipated that this programme will eventually lead to improvement in the delivery of FAIS care, reduce social and healthcare costs and assist in targeting and optimising patients much earlier in their clinical pathway.

**Ethics and dissemination**

This study raises no major ethical or legal issues.

The randomised study design will provide equal opportunities for all participants to treatment allocation. Each participant in the study will be given an opportunity to read and understand the study prior to signing the consent form and they will have the right to withdraw from the study at any time. The intervention will be delivered as a combination

of face-to-face and remotely using an app giving equal opportunities for patients who are unable to travel often. Reimbursements for their travel has been included and approved by the funding organisation.

Additionally, participation in the study will not alter their clinical pathway. Outcome measures will be taken at the time of their normal clinical visits reducing their visits to the hospital.

**Patient and Public Involvement (PPI)**

A focus group involving a patient and public panel informed the design of the study. An advisory group will be formed with 2 people from the PPI panel who will oversee the study. Several activities are planned with the PPI panel during the study as below;

1. Co-design the prehabilitation leaflet
2. Develop question guides for the research focus groups and semi structured interviews
3. Co-develop a training manual for clinicians
4. Design dissemination materials

**Strengths of the study**

- Interventions developed using a robust methodology (systematic review with meta-analysis and expert panel consensus)
- The first study to test the efficacy of a novel prehabilitation intervention in the FAIS group
- Randomised design and assessor blinding minimising selection, detection and performance biases.

